## Introduction

Osteoarthritis is the most common form of arthritis, and its prevalence is projected to increase by 75% by 2050 owing to population aging [1]. Characterized by pain, stiffness, progressive inflammation, and degeneration of articular cartilage [2], osteoarthritis imposes a substantial global socioeconomic burden [1]. As the disease advances, many patients with knee osteoarthritis require total knee arthroplasty (TKA), which is a procedure with increasing demand [1].

Patients with osteoarthritis exhibit significantly lower physical activity levels than healthy older adults [3]. In this context, prolonged TKA waiting times exacerbate inactivity, contributing to muscle weakness, functional decline [4], increased comorbidities, and poorer recovery [5]. Importantly, low preoperative functional capacity is associated with poor recovery, increased surgical complications, prolonged hospital stay, and higher readmission rates, further straining healthcare systems [6].

To mitigate these issues, clinical guidelines recommend preoperative exercise programs to improve postoperative recovery. Prehabilitation enhances physical readiness for surgery, improving their ability to tolerate surgical stress, potentially improving pain management, functional capacity, and quality of life [7]. In this regard, home-based exercise programs offer a viable alternative to in-person rehabilitation by overcoming barriers such as financial constraints and limited access [8]. Notably, supervised home-based interventions demonstrate comparable efficacy to in-person rehabilitation in improving pain and function [9].

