Patients will be excluded if they fail to attend scheduled telerehabilitation sessions or respond to WhatsApp communication. Those experiencing unexpected medical complications, such as infections or cardiac or respiratory events, will be instructed to discontinue the program and withdraw from the study. The exclusion criteria also included changes in clinical status leading to surgical contraindications or new injuries during the prehabilitation period that prevented participation in home exercises. Additionally, participants with cognitive deficits were excluded based on the Portuguese version of the Mini-Mental State Examination (MMSE), with cut-off scores of ≤20 for illiterate individuals, ≤25 for primary school level, ≤26.5 for junior high school, ≤28 for high school, and ≤29 for higher education [15].

Randomization

After the explanatory meeting, eligible participants who complete baseline assessments will be randomized using simple randomization with a 1:1 allocation ratio via Randomizer® (www.randomizer.org). The allocation sequence will be generated by an independent researcher not involved in enrollment or assessment. Allocation concealment will be ensured using sequentially numbered, opaque, sealed envelopes, which will be opened only after confirming participant eligibility.

Control group

The participants in the control group will receive an institutional educational booklet containing standard preoperative physiotherapy recommendations. The only exercise instructions before TKA provided in the booklet were as follows: “(1) Move your feet up and down 20 times (active movement while lying on a treatment table, plantar dorsiflexion) and (2) inhale deeply through your nose while raising your arms and exhale through your mouth as you lower them. Perform 20 repetitions.” Participants in the control group will only follow these institutional procedures and will not engage in a home-based program. They will be instructed to maintain their usual daily activities and adhere to the recommendations provided in the booklet.

Experimental group

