Osteoarthritis progression involves subchondral bone alterations, which exercise may counteract by preserving cartilage and bone integrity [14,20]. Bone cartilage fragments (distal femur condyle and tibial plateau) will be collected post-osteotomy, stored in sterile tubes, and processed for mitochondrial activity assays and immunohistochemical analysis of extracellular matrix structure. Markers include fibronectin type III domain-containing 5 (FNDC5), β-galactosidase (senescence marker), Bcl-2-associated X protein (BAX), and cytochrome C (Cyt-C). These markers will provide insights into mitochondrial function, programmed cell death, and cartilage remodeling, helping evaluate the local physiological response to the exercise program. Mitochondrial membrane permeability will be assessed using flow cytometry (Mitochondrial Membrane Potential Kit, MAK160, Merck). Due to considerable inter-individual variability and limited evidence directly connecting these biomarkers to prehabilitation in OA, FNDC5/irisin and β-galactosidase levels should be interpreted as exploratory outcomes. Effect sizes are expected to be small to moderate. Nevertheless, FNDC5 has demonstrated chondroprotective mechanisms in OA models, including enhanced cartilage integrity and reduced chondrocyte apoptosis [24], supporting its inclusion to explore metabolic and cellular adaptations to exercise.

Self-reported pain, stiffness, knee function, and anthropometric measurement

The Western Ontario and McMaster Universities Arthritis Index (WOMAC), a validated tool for knee osteoarthritis and post-TKA patients, assesses pain (5 items, 0-20 points), stiffness (2 items, 0-8 points), and physical function (17 items, 0-68 points) [25]. The total score is obtained by summing the individual scores and can be converted to a 0-100 scale, with higher values indicating greater impairment. Body mass will be measured using the Líder® P150C digital scale (São Paulo, Brazil). Height will be assessed using a Ghrum Polar Manufacture Instruments® anthropometer (Geneva, Switzerland). Waist circumference will be measured with Sanny® anthropometric tape (São Paulo, Brazil). Both the WOMAC and the anthropometric measurements will be performed at three moments: multidisciplinary consultation, pre-hospitalization, and 30-day follow-up consultation.

Prehabilitation adherence

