## Results

The significance level was set at p < 0.05, and analyses will be performed using IBM SPSS Statistics 21.0 (IBM®, Armonk, NY, USA). Data normality will be assessed using the Shapiro-Wilk test. Baseline demographic characteristics will be compared between the groups using independent t-tests (normal data), Mann-Whitney U tests (non-normal data), and chi-square or Fisher’s exact tests (categorical variables).

The primary outcome, changes in plasma CRP levels across four time points (nine weeks pre-TKA, one day pre-TKA, three days post-TKA, and 30 days post-TKA), and WOMAC scores across three time points (baseline, one day pre-TKA, and 30 days post-TKA) will be analyzed using two-way repeated-measures ANOVA (group × time interaction), contingent upon assumptions of normality and sphericity. If these assumptions are violated, linear mixed models (LMM) or generalized estimating equations (GEE) will be employed as more robust alternatives, capable of handling missing data and irregular intervals. Post-hoc pairwise comparisons will use the Bonferroni correction to adjust for type I errors. For non-parametric repeated measures, the Friedman test will be used, followed by Dunn-Bonferroni post-hoc tests when applicable.

Secondary outcomes, including synovial fluid and tissue biomarkers, hospital outcomes (length of stay, complications, readmissions), and satisfaction scores at specific time points, will be compared between groups using independent t-tests (normal data) or Mann-Whitney U tests (non-normal data). Correlations between biomarkers, hospital outcomes, WOMAC scores, and satisfaction will be examined using repeated measures correlation (rmcorr) for normal data or generalized linear mixed model (GLMM) for non-normal data. Rmcorr will be applied when assessing the strength and direction of associations between two continuous variables measured repeatedly within individuals. GLMM will be used in cases requiring the modeling of random effects, adjustment for covariates, or handling of non-normal or categorical outcomes, ensuring analytic flexibility across diverse data structures. To account for multiple comparisons in biomarker and exploratory analyses, false discovery rate (FDR) adjustment will be applied where appropriate.

Effect sizes (e.g., partial eta-squared for ANOVA and Cohen’s d for pairwise tests) and 95% confidence intervals will be reported alongside p-values to enhance the clinical interpretability of findings.

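### Length of stay and satisfaction are compared by unadjusted two-sample tests although prognostic baseline values are collected before randomisation: valid, but some precision is given up

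*Protocol article*

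**What the plan says.** All references are to the protocol article.

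- **Analysis (Results).** The rule covers "Secondary outcomes, including synovial fluid and tissue biomarkers, hospital outcomes (length of stay, complications, readmissions), and satisfaction scores at specific time points". These "will be compared between groups using independent t-tests (normal data) or Mann-Whitney U tests (non-normal data"). No covariate is named.
- **Allocation (Randomization).** Participants are "randomized using simple randomization with a 1:1 allocation ratio via Randomizer". No strata, blocks or minimisation are described. Baseline data come first: "eligible participants who complete baseline assessments will be randomized".
- **Baseline data (section on self-reported pain, stiffness, knee function and anthropometry).** "Both the WOMAC and the anthropometric measurements will be performed at three moments: multidisciplinary consultation, pre-hospitalization, and 30-day follow-up consultation". Mass and height are both measured. BMI is not named but follows from them. Age and sex are known at enrolment (Enrollment).
- **Prognosis (Introduction).** The article states that "low preoperative functional capacity is associated with poor recovery, increased surgical complications, prolonged hospital stay, and higher readmission rates".
- **Other uses of baseline or covariate information.** Results compares baseline characteristics between arms by significance tests. Covariate adjustment is mentioned once, as a use of the generalized linear mixed model in the account of the correlation analyses, with no covariate named. The sensitivity analyses under Strengths and limitations give adherence, engagement and expectancy as examples, and none of these is one of the baseline variables above.

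**The concern.** CRP and WOMAC are analysed with their own baseline value in a repeated-measures model. Length of stay and satisfaction are observed once, after surgery, and have no baseline of their own. Baseline information can enter their comparison only through covariates, and the stated tests use none.

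The article itself supplies a reason to expect a gain. It names preoperative function as related to hospital stay and recovery, and it measures self-reported function before allocation. Variance in the outcome that these variables explain stays in the error term. The trial is sized on CRP and states no power for these outcomes, so precision that needs no further data collection is worth having.

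**Working it through.** **Plan's own figure.** The article gives no power or detectable difference for length of stay or satisfaction, so there is nothing to reproduce. Its sample size (78, or 86 with attrition) was set for CRP. It is used here only as the number available.

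**Inputs**
- n = 78 / 2 = 39 per arm (Sample size). Simple randomisation does not guarantee equal arms; equality is assumed.
- α = 0.05 (Results). Sidedness is not stated; two-sided is assumed.
- True difference d = 0.5 SD. Assumed; the documents give no target for these outcomes.
- R², the share of outcome variance explained by baseline WOMAC function, age, sex and BMI. Not in the documents; 0.05 to 0.30 assumed.

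**Formula.** Adjustment multiplies the residual SD by √(1 − R²). Power comes from the noncentral t distribution with noncentrality

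δ = [d / √(1 − R²)] × √(n/2).

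Degrees of freedom are 2n − 2 = 76 unadjusted, and 76 − 4 = 72 with four covariates. The equivalent unadjusted total is 78 / (1 − R²).

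Unadjusted: δ = 0.5 × √19.5 = 2.208. For R² = 0.20: δ = 2.208 / √0.80 = 2.469.

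| R² (assumed) | δ | Power at d = 0.5 | Difference detectable with 80% power | Equivalent unadjusted N |
|---|---|---|---|---|
| none (unadjusted) | 2.208 | 58.7% | 0.643 SD | 78 |
| 0.05 | 2.265 | 60.8% | 0.627 SD | 82 |
| 0.10 | 2.327 | 63.2% | 0.610 SD | 87 |
| 0.20 | 2.469 | 68.3% | 0.575 SD | 98 |
| 0.30 | 2.639 | 74.0% | 0.538 SD | 111 |

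With 43 per arm (86 / 2, no attrition), power goes from 63.0% unadjusted to 65.2%, 67.5%, 72.6% and 78.2%.

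**Is chance imbalance a second cost?** The arm difference in a standardised baseline variable has SD √(2/39) = 0.226, so its 95% range is ±0.44 SD. If that variable correlates 0.3 with the outcome (assumed), an imbalance of 0.44 SD moves the unadjusted difference by 0.44 × 0.3 = 0.13 SD. The standard error of the unadjusted difference is itself √(2/39) = 0.226 SD, and it already includes this source of variation. The (1 − R²) factor in the table is the gain from removing it, so it must not be counted again.

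**The case against.** **The unadjusted test is valid.** This stands. In a randomised trial, chance imbalance is random error that the standard error covers. A reader might infer that simple randomisation with an unadjusted test leaves the result biased, or that imbalance is a harm on top of lost precision. The documents support neither reading: there is one cost, precision.

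**The synovial and tissue markers.** The same sentence in Results covers them, so a reader might extend the point to them. Nothing in the article says that function, age, sex or BMI predicts these markers. The Tissue biomarkers section stresses their large variability between individuals and calls some of them exploratory. They are not part of this point.

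**The size is assumed.** This also stands. Neither R² nor d = 0.5 is in the documents. The Introduction speaks of functional capacity, which is not the same as self-reported WOMAC function, and gives no strength of association. It names hospital stay directly, but satisfaction only by way of recovery in general. At R² = 0.05 the gain is about two points of power. The figures are for a linear model and do not carry over exactly to the Mann-Whitney test.

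**An article condenses, and covariate lists may sit in an analysis plan.** This stands only in part. The article does not leave the comparison open: it names the tests. Its one mention of covariate adjustment belongs to the correlation analyses. The examples of confounders for sensitivity analyses are open-ended, so supplementary adjustment is not ruled out, but none is committed to.

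**Only secondary outcomes are affected.** True. The CRP and WOMAC analyses are untouched.

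**Conclusion.** The point holds as a matter of efficiency for length of stay and satisfaction. The article fixes a covariate-free comparison while holding pre-randomisation variables, at least one of which it describes as prognostic. At 39 per arm and d = 0.5, adjustment would add between about 2 points of power (58.7% to 60.8%, R² = 0.05) and about 15 points (to 74.0%, R² = 0.30). That corresponds to an unadjusted trial of 82 to 111 patients instead of 78. The range rests on the assumed R² and d, equal arms, a two-sided 5% level, and a scale on which a linear model fits reasonably. Validity is not in question, and no conclusion on the primary outcome depends on this.

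**What to change.** In Results, take length of stay and satisfaction out of the t-test / Mann-Whitney sentence and prespecify as the main comparison:

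- **Length of stay:** linear regression of log days on arm, baseline WOMAC function, age, sex and BMI.
- **Satisfaction:** linear regression of the total score on the same terms.

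Use only the values from the nine-week multidisciplinary consultation. The pre-hospitalisation WOMAC comes after randomisation, may itself be changed by the programme, and should not be a covariate. Name the covariates now, so that the planned baseline significance tests do not decide which are used. Keep the unadjusted test as a sensitivity analysis.

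The cost is wording only, since mass and height give BMI and the other variables are already recorded. The price is about four degrees of freedom, a model in place of a two-sample test, and a length-of-stay effect reported as a ratio of geometric means, which the text should say.

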Adherence to the prehabilitation program will be assessed by calculating the percentage of completed sets compared to the total prescribed sets. This information will be recorded in the training diary and reported by the patient or a family member. The number and classification of adverse events occurring during the home-based training period will be recorded separately from hospital outcomes.

Adherence will be operationally defined as the completion of ≥75% of prescribed sessions, based on adherence rates commonly reported in the literature. A recent systematic review by Adebero et al. [7] found that most prehabilitation trials achieved adherence rates of 74% or higher, supporting the use of this threshold. This cutoff will be used to determine eligibility for per-protocol analyses evaluating intervention efficacy, while all randomized participants will be retained in the dose-response analysis, regardless of adherence level.

Hospital outcomes

Hospital outcomes will include the length of hospital stay (in days), hospital readmission rate, and number and classification of complications occurring within 30 days post-surgery. These indicators were selected to complement the biological and functional recovery metrics, offering system-level proxies for early recovery quality. Specifically, reduced length of stay may reflect improved physiological readiness for discharge, while lower readmission and complication rates may signal enhanced resilience and postoperative recovery. These data will be retrieved from patients’ medical records, which will be accessed using the registration number recorded during patient enrollment. Surgical complications will be defined as any adverse events based on the Clavien-Dindo classification [26].

Satisfaction level

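### Readmission, a yes/no outcome, is assigned to a t-test or Mann-Whitney test, and no risk-scale effect is specified for it

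*Protocol article*

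**What the plan says.** The Hospital outcomes subsection of Materials and methods lists length of stay together with "hospital readmission rate, and number and classification of complications occurring within 30 days post-surgery". It adds that "Surgical complications will be defined as any adverse events based on the Clavien-Dindo classification", and it speaks of lower readmission and complication rates as possible signs of better recovery.

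The Results section gives the analysis. For the group comparison, "hospital outcomes (length of stay, complications, readmissions), and satisfaction scores at specific time points, will be compared between groups using independent t-tests (normal data"), and otherwise "or Mann-Whitney U tests (non-normal data). Correlations between biomarkers, hospital outcomes, WOMAC scores, and satisfaction" (the second half of that quote opens the next sentence, on correlations). Normality is judged by Shapiro-Wilk.

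Categorical tests appear once, for baseline data: "Baseline demographic characteristics will be compared between the groups using independent t-tests (normal data), Mann-Whitney U tests (non-normal data), and chi-square or Fisher’s exact tests" for categorical variables. On effect measures the section says "Effect sizes (e.g., partial eta-squared for ANOVA and Cohen’s d for pairwise tests) and 95% confidence intervals will be reported" alongside p-values.

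**The concern.** Readmission is binary per patient and is described as a rate. The stated rule nevertheless sends it through a normality check to a t-test or a rank test. The protocol's own tools for such data, "chi-square or Fisher’s exact tests (categorical variables"), are reserved for describing the groups at baseline. This is not detail left out of a condensed article: the outcomes are named and a specific test is assigned to them.

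Two things are at stake. With few events in about 40 patients per arm, whether p falls below 0.05 can depend on which test is run. And a reader who wants to know how many readmissions or complications were avoided is offered a standardised mean difference as the example effect size, with no risk difference, risk ratio or odds ratio named. The Discussion lists complications and readmission rates among the secondary objectives, so these comparisons will be interpreted.

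**Working it through.** **Inputs.** The Sample size subsection gives 78 evaluable participants and a target of 86 after 10% attrition; 78 × 1.10 = 85.8, which rounds up to 86. With 1:1 allocation this is about 39 evaluable or 43 randomised per arm. Simple randomization makes equal arms an approximation. Alpha is 0.05, taken as two-sided. The documents give no event rates, so all event counts and rates below are illustrative.

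**Step 1. Which test does the rule select?** Shapiro-Wilk on 0/1 data at this size always points away from normality: for 3 events in 43, p = 3 × 10⁻¹³; for 21 in 43, p = 4 × 10⁻⁹. So the rule leads to Mann-Whitney.

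**Step 2. What is Mann-Whitney on 0/1 data?** With a and b events in two arms of n, K = a + b and N = 2n, Pearson's statistic is X² = N[a(n − b) − b(n − a)]² / [n²K(N − K)]. The tie-corrected Mann-Whitney z² equals X² × (N − 1)/N. For 0 versus 4 of 39:

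- X² = 78 × (4 × 39)² / (39² × 4 × 74) = 4.216, p = 0.040.
- Mann-Whitney z² = 4.216 × 77/78 = 4.162, p = 0.041.
- Fisher p = 2 × C(39,4)/C(78,4) = 2 × 82,251/1,426,425 = 0.115.

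**Step 3. Other sparse tables, two-sided p** (Mann-Whitney is asymptotic, without continuity correction)

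| Events | Per arm | t-test | Mann-Whitney | Chi-square | Fisher |
|---|---|---|---|---|---|
| 0 v 4 | 39 | 0.041 | 0.041 | 0.040 | 0.115 |
| 1 v 7 | 39 | 0.025 | 0.026 | 0.025 | 0.056 |
| 2 v 8 | 39 | 0.043 | 0.043 | 0.042 | 0.087 |
| 0 v 4 | 43 | 0.041 | 0.042 | 0.041 | 0.116 |
| 1 v 7 | 43 | 0.026 | 0.027 | 0.026 | 0.058 |
| 2 v 8 | 43 | 0.044 | 0.045 | 0.044 | 0.089 |

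**Step 4. Is the planned test anticonservative?** True size is the sum, over all pairs (a, b) with p < 0.05, of Bin(a; n, π) × Bin(b; n, π), with the same event rate π in both arms.

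| Event rate | Mann-Whitney, 39 | Fisher, 39 | Mann-Whitney, 43 | Fisher, 43 |
|---|---|---|---|---|
| 2% | 0.7% | 0.01% | 0.9% | 0.02% |
| 5% | 4.2% | 0.4% | 4.7% | 0.5% |
| 8% | 5.8% | 1.1% | 6.0% | 1.4% |
| 10% | 5.9% | 1.6% | 5.9% | 1.9% |
| Maximum, rates up to 50% | 5.9% | 3.1% | 6.0% | 3.2% |

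The planned test exceeds 5% by about one point at worst, while Fisher lies well below 5%. Most of the gap in step 3 is therefore Fisher's conservatism.

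**Step 5. Cohen's d on 0/1 data.** With proportions p₁ and p₂ in equal arms, d ≈ (p₂ − p₁) / √{[p₁(1 − p₁) + p₂(1 − p₂)]/2}. The same 10-point risk difference gives:

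- 0% v 10%: 0.10/√0.045 = 0.47
- 10% v 20%: 0.10/√0.125 = 0.28
- 40% v 50%: 0.10/√0.245 = 0.20

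So d more than doubles with the base rate while the absolute effect stays the same.

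**Step 6. What a risk-scale summary would show.** For 0 v 4 of 39 the risk difference is 4/39 = 10.3 points. The Newcombe interval combines the two Wilson intervals (l₁, u₁) and (l₂, u₂): lower limit = (p₂ − p₁) − √[(p₂ − l₂)² + (u₁ − p₁)²], upper limit = (p₂ − p₁) + √[(u₂ − p₂)² + (p₁ − l₁)²]. It runs from −0.6 to 23.6 points and includes zero, although the planned test gives p = 0.041.

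**The case against.** Five arguments on the other side have weight.

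- **Complications.** A reader might infer that all the hospital outcomes are misassigned. The documents do not support that. Complications are recorded as a number and a Clavien-Dindo class; Mann-Whitney is a standard test for ordinal grades and usable for counts. The article lists no any-complication endpoint as such; it only speaks of complication rates. This stands: the point reaches readmission and any comparison of proportions with a complication, and no further.
- **False positives.** A reader might infer that the planned test produces spurious significance. It does not to any material degree: its size peaks at about 6% and is below 5% at event rates of 5% or less. Chi-square, which the protocol itself names, gives nearly the same p-values. This stands. It is tempered by the expected counts of 2 and 4 events per arm in the 0 v 4 and 1 v 7 tables, below the usual threshold of 5 at which Fisher is preferred.
- **Exact or asymptotic.** The article does not say which Mann-Whitney is meant. The exact version on 0 v 4 of 43 gives 0.116, the same as Fisher. This stands, and is another reason to name the test.
- **Effect size.** A reader might infer that no interpretable effect will be reported. That is too strong: Cohen's d is only an example, 95% intervals are promised, and the mean difference of a 0/1 variable is the risk difference. What remains is that the one example given for pairwise tests is unsuitable for a binary outcome and no risk-scale measure is specified.
- **GLMM.** The text says that "GLMM will be used in cases requiring the modeling of random effects, adjustment for covariates, or handling of non-normal or categorical outcomes". This does not repair the assignment, because it elaborates the correlation analyses; the group comparison has its own sentence with its own two tests.

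**Conclusion.** Wrong as written, minor. The article assigns a binary outcome to tests for continuous or ranked data, although it names suitable categorical tests for baseline variables. The practical loss is mainly in reporting: Cohen's d for the same 10-point difference ranges from 0.47 to 0.20 depending on the base rate. The effect on significance is secondary. In sparse tables such as 0 v 4 of 39 the planned asymptotic test and Fisher fall on opposite sides of 0.05 (0.041 v 0.115), but the planned test's true size is no more than about 6%.

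These figures assume 39 to 43 patients per arm, two-sided testing, the asymptotic Mann-Whitney test, and event counts chosen for illustration. Nothing in the documents shows how likely such tables are. Readmission and complications are secondary outcomes; the CRP analysis and the sample size do not depend on them.

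**What to change.** Amend the secondary-outcome sentence in the Results section. For readmission and for any complication within 30 days, report counts per arm, the risk difference with a 95% score (Newcombe) interval, and Fisher's exact test, or chi-square when expected counts allow, with the threshold stated. Do not use a t-test, Mann-Whitney or Cohen's d for these two. Keep Mann-Whitney for Clavien-Dindo grade, complication counts, length of stay and other non-normal outcomes.

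The cost is a sentence or two of wording and no extra data. Exact p-values will be somewhat less favourable. The score interval and Fisher can also disagree: for 1 v 7 of 39 the Newcombe interval is 1.5 to 30.3 points while Fisher gives 0.056. The sentence should therefore say in advance which of the two carries the interpretation.
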